### Variables and instruments

3.4

The variables measured in this project, the instruments used and the informants who will complete each measure are detailed below:

Socio-demographic (sex, age, patient’s level of studies, parents’ level of studies) and clinical variables (current pharmacological treatment—active substance and dose). These data will be collected with an initial survey created *ad hoc* for the present study.Processing speed. The Symbol Digit Modalities Test (SDMT) (Smith, 2002) will be administered to patients.Visual sustained attention/vigilance. The Kiddie Continuous Performance Test, second edition (K-CPT 2) (Conners, 2006) will be administered to children aged 4 to 7 years, and the Continuous Performance Test, third edition (CPT 3) (Conners, 2014) to children aged 8 and above. This test computes several scores, as follows: Detectability, Omissions, Commissions, Perseverations, Hit Reaction Time (HRT), HRT Standard Deviation, Variability, HRT Block Change and HRT Inter-Stimulus Interval Change.Immediate and delayed verbal memory. A Spanish test based on the California Verbal Learning Test will be administered to patients. Specifically, the Spain-Complutense Verbal Learning Test for Children (TAVECI) (Benedet et al., 2017) will be administered to children aged 3 to 16 years; and the version for older patients (TAVEC) (Benedet and Alejandre, 2014) will be applied to adolescents aged 16 to 18 years. This test allows calculating a wide range of scores regarding the verbal memory performance, and the following scores will be specifically used in this study: Immediate Recall, Short Delay Free Recall, Short Delay Cued Recall, Long Delay Free Recall, Long Delay Cued Recall, Long Delay Recognition, Semantic clustering strategies, Serial clustering strategies, False positives, and Discriminability.Semantic memory. The Vocabulary subtest of the Wechsler Intelligence Scale for Children, fifth edition (WISC-V) (Wechsler et al., 2015) will be administered to patients up to the age of 16.11 years, and the adult version, fourth edition (WAIS-IV) (Wechsler, 2012), will be applied to patients up to 18 years.Verbal working memory and cognitive flexibility. The Digit Span subtest of the WISC-V (Wechsler et al., 2015) or the WAIS-IV version (Wechsler, 2012) will be administered to patients. Three neurocognitive domain-specific scores will be considered from the three differentiated parts of the task (Forward, Backward, and Sequencing subscales), as well as the global score (Digit Span) as a measure of cognitive flexibility (Wechsler et al., 2015).Verbal fluency. The Verbal Fluency Test (TFV) (Portellano Pérez and Martínez Arias, 2020) will be administered to patients. This test calculates the following eight scores: Phonological fluency, Semantic fluency, Excluded-letter fluency, Total Fluency Index, Errors in phonological fluency, Errors in semantic fluency, Errors in excluded-letter fluency and Total errors.Ability to inhibit cognitive interference. The Stroop Colour Word Test (SCWT) (Golden, 2020) will be administered to patients. Four scores can be computed from this test, such as: the Word reading (W), the Colour naming (C), the Colour-word (CW) and Resistance to Interference.Visuo-constructive organizational ability and immediate and delayed visual memory. The Rey-Osterrieth Complex Figure (ROCF) test (Rey, 2003) will be applied to patients. This test generates four scores: a copy score (accuracy in terms of visual–spatial constructional ability), the time required to copy the figure, and two delayed-recall scores (at 3 and 30 min).Non-verbal Intelligence. The Test of Non-verbal Intelligence, fourth edition (TONI-4) (Brown et al., 2019), using both parallel forms (A and B), will be administered to patients.Ecological Executive Functioning. The Behavior Rating Inventory of Executive Function, second edition (BRIEF-2) (Maldonado-Belmonte et al., 2017), in its parent-reported version, will be completed by the patient’s parents (or legal guardians).Emotional and behavioral problems. The Behavioral Assessment System for Children and Adolescents, third edition (BASC-3) (Reynolds and Kamphaus, 2020) will be administered, both the parent-reported version, by the patient’s parents (or legal guardians), and the self-reported version, by the patient. This questionnaire covers the personal (e.g., adaptive skills, resiliency, externalizing, and internalizing problems) and interpersonal/social domains (e.g., school problems, relationships with parents, interpersonal relations) of each patient.Pain intensity and interference. The Brief Pain Inventory (BPI) (Badia et al., 2003) will be used as a self-reported measure by patients. This questionnaire includes questions (from 0 to 10 referring to the last seven days) covering two dimensions: pain intensity (worst and mildest pain in the week, average pain, and current pain), and pain interference (general activity, mood, walking, school, sleep, as well as enjoyment of life).Sleep problems. The PROMIS Pediatric Sleep Disturbances Short Form (Forrest et al., 2018) will be used as a self-reported questionnaire by patients. It is a 4-item questionnaire that assesses problems of sleep onset and maintenance in the last 7 days.Insomnia. The Adolescent Insomnia Questionnaire (AIQ) (Bromberg et al., 2020) will be used as a self-reported measure by patients. It is a 13-item questionnaire that covers three domains: Sleep Dissatisfaction and Impairments, Sleep Onset, and Sleep Maintenance.Adherence to treatment. The Simplified Medication Adherence Questionnaire (SMAQ) (Ortega Suárez et al., 2011) will be used to evaluate therapeutic adherence as a self-reported measure. Also, blood levels of the prescribed drugs (mainly immunosuppressants) will be used to objectively evaluate therapeutic adherence, which will be extracted from the clinical history of each patient.

Table 1 summarizes the measurement instruments used, the domains covered by each instrument, as well as the informants who will complete each measure.

**Table 1 tab1:** Variables and instruments of the project: dimensions measured, test and informants.

Dimensions measured	Test	Ages	Informant
-Socio-demographic data. -Medication: active ingredient and dose.	Survey created *ad hoc* for this project.	6–18 years old	Parent/guardian
**Neuropsychological domains**			
Processing speed	*-Symbol Digit Modalities Test* (SDMT) (Smith, 2002).	6–85 years old	Patient
Visual sustained attention/vigilance	*-Kiddie Continuous Performance Test, 2nd edition* (K-CPT 2) (Conners, 2006). *-The Continuous Performance Test, 3rd edition* (CPT 3) (Conners, 2014).	4–7 years old 8–83 years old	Patient
Immediate and delayed verbal memory	*-España-Complutense Verbal Learning Test for Children* (TAVECI) (Benedet et al., 2017). *-España-Complutense Verbal Learning Test* (TAVEC) (Benedet and Alejandre, 2014).	3–16 years old 16 – adults	Patient
Semantic memory	*-Vocabulary of the Wechsler Intelligence Scale for Children-V* (WISC-V) (Wechsler et al., 2015). *-Vocabulary of the Wechsler Intelligence Scale for Adults-IV* (WAIS-IV) (Wechsler, 2012).	6–16:11 years old 16–90 years old	Patient
Verbal working memory and cognitive flexibility	*-Digit Span of the Wechsler Intelligence Scale for Children-V* (WISC-V) (Wechsler et al., 2015). *-Digit Span of the Wechsler Intelligence Scale for Adults-IV* (WAIS-IV) (Wechsler, 2012).	6–16:11 years old 16–90 years old	Patient
Verbal fluency	*-Verbal Fluency Test* (TFV) (Portellano Pérez and Martínez Arias, 2020).	6 years old – adults	Patient
Ability to inhibit cognitive interference	*-Stroop Colour Word Test* (SCWT) (Golden, 2020).	6–85 years old	Patient
Visuo-constructive organization/planning and immediate and delayed visual recall	*-Rey-Osterrieth Complex Figure* (ROCF) (Rey, 2003).	6–80 years old	Patient
Non-verbal abstract reasoning	*-Test of Non-verbal Intelligence- 4* (TONI-4), parallel forms A and B (Brown et al., 2019).	6–79 years old	Patient
-Global executive function -Behavioral regulation -Emotional regulation -Cognitive regulation	*-Behavior Rating Inventory of Executive Function, 2nd edition* (BRIEF-2) (Maldonado-Belmonte et al., 2017).	5–18 years old	Parent/guardian
**Mental health, pain, sleep problems and therapeutic adherence**			
*Parent-reported version:* *-Adaptive skills*. *-Behavioral symptom index*. *-Externalizing problems*. *-Internalizing problems*. *Self-reported version:* *-Personal adjustment*. *-Inattention/Hyperactivity*. *-Internalization problems*. *-School problems*. *-Emotional symptoms index*.	*-Behavioral Assessment System for Children and Adolescents − 3* (BASC-3) (Reynolds and Kamphaus, 2020).	3–18:11 years old 8–18:11 years old	Parent/guardian Patient
-Pain intensity. -Pain interference.	*-Brief Pain Inventory* (BPI) (Badia et al., 2003).	6 years old – adults	Patient
Quality of sleep	-*PROMIS Pediatric Item Bank*. *Sleep Disturbance – Short Form 4a* (Forrest et al., 2018).	5–17 years old	Patient
-Dissatisfaction with sleep and deterioration. -Sleep onset. -Sleep maintenance.	-*Adolescent Insomnia Questionnaire* (AIQ) (Bromberg et al., 2020).	11–18 years old	Patient
-Taking prescribed medication. -Application of other prescribed guidelines. -Attendance at clinical consultations.	*Simplified Medication Adherence Questionnaire* (SMAQ) (Ortega Suárez et al., 2011).	6–18 years old	Patient
Adherence to prescribed treatments	Blood levels of prescribed drugs (mainly immunosuppressants), which will be taken from each patient’s medical history.	6–18 years old	Patient

### Procedure

3.5

The fieldwork for this study will take place at La Paz University Hospital (Madrid, Spain) and it will be conducted by clinical psychologists trained in neuropsychological testing ([name] and [name]).

First of all, patients and their parents (or legal guardians) will be briefly informed about this study by medical/surgical professionals and, if they agree, they will be referred to the Psychiatry, Clinical Psychology and Mental Health Unit at the Children hospital. This Mental Health team will inform the patients and/or their legal guardians, in a more exhaustive manner, about the objectives of the present study. An initial screening will be carried out to examine compliance with the inclusion/exclusion criteria and, if so, they will be given the information and informed consent forms. After authorization and consent to participate in this study, they will be sent electronic links to complete the battery of questionnaires, in which they will be identified with an anonymous code in order to preserve their identity under the strictest confidentiality; and, subsequently, the neuropsychological testing will begin. The neuropsychological assessment will be carried out in person and individually with each patient; while the digitalised assessment will require 4 types of links across the different platforms, from REDCap (Harris et al., 2009), Hogrefe TEA Ediciones and Pearson Clinical, for the self- and parent/legal guardians-reported questionnaires. Post-transplant evaluations will take place at 4 weeks and 6 months after transplantation. In these two post-transplant phases, the same type of tests and questionnaires described in the previous phase will also be administered, although with a shorter battery at 4 weeks. At each stage of the neuropsychological evaluation, tests will be administered during a single session. Sessions during the pre-transplant and the 6-months follow-up phases will have a duration of approximately one and a half to maximum 2 h (including a 10-min break). Testing at 4 weeks after transplantation will be of a shorter duration, around 45 min. After each assessment, the clinical psychologists will enter the data into the project database.

This study follows a mixed-methods approach: a quantitative methodology following an observational cohort design, based on standardized tests and questionnaires; as well as a qualitative methodology, based on focus groups.

On the one hand, the quantitative evaluations will take place in both pre- and post-transplantation phases. Specifically, the assessment in the pre-transplant phase will take place, when possible, within 0–6 months prior to the transplantation, as recommended by expert consensus (Kaustov et al., 2021). The post-transplantation phases will take place at 4 weeks and 6 months after the surgery.

Additionally, the patients’ parents (or legal guardians) will also have to authorize, in an informed manner, the participation of their children, as well as themselves in focus group sessions to qualitatively identify unmet care needs during the pre-, and post-transplant phases. Another focus group will also involve medical/surgical professionals of transplant recipients. There will be a total of 3 group sessions lasting up 90 min each (or until arriving at theoretical sufficiency), one session per participant type (patients, parents/guardians, and clinicians), 5 participants each group (*n* = 15 in total). All these focus groups will follow a biopsychosocial theoretical framework. Specifically, each focus group will begin indicating the group norms (confidentiality/privacy, not interrupting others’ turn to speak and not judging others’ comments). Afterwards, the session will continue with a first part of open questions about what aspects would have changed or improved in the health care, both for the patients and their parents, during the whole transplantation process. Subsequently, the second part of the focus group will pose specific questions about biomedical, psychological and social aspects that would have improved throughout the transplantation process and were not spontaneously addressed in the first part of each focus group. The sessions will be conducted by videocall, audio-recorded and automatically transcribed, respecting the confidentiality of the information at all times. The sessions will be facilitated by a member of the research team, different from the PI of this project ([name]) to avoid biases (the PI knows most transplant clinicians, patients and their parents/legal guardians). The facilitator will be a psychologist, female, with Master’s Degree credentials. The automatically-generated transcriptions will be reviewed by the group facilitator present in the session in order to: (1) change the name of the participants by a code, and (2) correct any transcription mistakes. The recordings will be kept until it has been verified that the transcription process has been carried out correctly. Transcripts will not be returned to participants for comments. If needed, in anticipation that more relevant information may be collected, participants will be offered the possibility of individual in-depth interviews after the focus group. These interviews will be conducted under the same above-mentioned standards.

Finally, the results from this project will be disseminated and published in different scientific media and documents, both written (articles in specialized journals, posters at conferences) and oral (presentations at conferences).

The protocol of this study was registered at clinicaltrials.gov on July 1, 2022 (NCT05441436).

Figure 1 lists the phases of the study, as well as the variables and instruments in each phase.

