### Statistical analyses

3.6

The data will be processed primarily using the statistical software IBM SPSS Statistics 29, among others, and mainly the following analyses will be performed:

First, descriptive analyses will be carried out for all variables to identify possible errors or outliers in dataset. Then, zero order correlation analyses will be computed to determine the degree of association between variables; and partial correlation analyses will be conducted to examine its association excluding the effect of other confounding variables.

Additionally, as main statistical analysis, a mixed Analysis of Covariance will be performed to evaluate the main effects between groups (2 types of transplant: solid organ and haematopoietic) and within groups (time variable with 3 levels: pre-, post-transplantation at 4-weeks and 6-months follow-up) as well as potential interactive effects, excluding the effect of confounding variables. *P*-value adjustments for multiple comparison will be performed. In turn, other analytical strategies will be used to examine time series such as latent grow models. Finally, innovative statistical analyses based on multiple linear regression will be developed to examine the relative weight of the different predictor variables on the criterion variables, already published elsewhere (Fernández-Jiménez and Arnett, 2015).

All these statistical analyses will be complemented with the appropriate effect size indexes for each statistical test (e.g., *f*, omega-square and *R^2^* indexes) (Cohen, 1992). Additionally, Reliable Change Index (RCI) will be computed in order to determine the real change of each individual score between measurements over time (Kiselica et al., 2023).

Since the main statistical analysis in this study will be a mixed Analysis of Covariance (2 × 3), with a statistical power = 0.95 and a risk/significance level of alpha = 0.05, to detect at least a moderate effect size (*f* = 0.25) on the outcome variables included, a minimum sample size of 36 patients will be required according to GPower 3.1.9.4 software.

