In short, the results of the pre- and post-transplant biopsychosocial and neuropsychological assessments will help to guide future clinical or educational interventions, if necessary, as well as to plan other activities to strengthen the patient’s resources, always with the aim of improving their personal, family, social and school adaptation. In the event that parents/legal guardians so request, clinical reports will be issued with recommendations that will help the patient’s educational centres to guide potential adaptations (curricular, assessment, or methodological) according to pedagogical criteria.

Among the methodological strengths of this study is the multi-method/multi-source approach, which includes not only self-/parent-reported questionnaires, but also objective neuropsychological tests and blood levels of prescribed drugs, thus avoiding common method bias (Podsakoff et al., 2012). These measures will constitute a multidomain set of outcomes that includes variables relevant to transplant recipients, their caregivers, and health professionals for decision making (Annema et al., 2023). However, our study presents several limitations. First, we will use a non-random sampling technique that increases the probability of some degree of collider bias and limits the generalizability of the findings. Second, because of the observational nature of the design, sound causal inferences cannot be drawn. Third, given the modest number of patients from the paediatric population undergoing a transplantation process, intergroup comparisons between types of solid organ transplants will be limited. Fourth, due to the clinical setting in which this project is implemented, other neurocognitive domains focused more specifically on school performance, such as reading or writing, will not be addressed. Last, attrition during post-transplantation or follow-up phases could bias the results because patients suffering more severe medical complications could be excluded from assessments, during the prefixed measurement times in this study.

Finally, the protocolisation of the assessment and monitoring of these clinical populations aims to create a working dynamic, of greater coordination between departments in our hospital, that will last beyond the years of this project, increasing the awareness among other clinicians about the potential neurocognitive and psychological needs of the patients and their relatives during the transplantation process.

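### The main 2 x 3 mixed ANCOVA does not fit tests left out of the shorter 4-week battery, and for the other tests it would keep only children with all three scores

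*Protocol article*

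**What the plan says.** Statistical analyses (3.6) states that "as main statistical analysis, a mixed Analysis of Covariance will be performed". The between-group factor is "2 types of transplant: solid organ and haematopoietic", and the within-group factor is a "time variable with 3 levels: pre-, post-transplantation at 4-weeks and 6-months follow-up". The sample size is set for this 2 x 3 layout at f = 0.25, "with a statistical power = 0.95 and a risk/significance level of alpha = 0.05", and the section concludes that "a minimum sample size of 36 patients will be required according to GPower 3.1.9.4 software". Planned enrolment is 60. The section does not restrict the three-level model to tests given at all three visits. It names latent growth models only as a further strategy.

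Procedure (3.5) says the same kinds of tests and questionnaires are repeated after transplant, "although with a shorter battery at 4 weeks". The 4-week session lasts around 45 minutes; the pre-transplant and 6-month sessions last one and a half to two hours. The Abstract says, without exception, that the outcomes are measured at all three time points.

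The Discussion lists as a limitation that "attrition during post-transplantation or follow-up phases could bias the results because patients suffering more severe medical complications could be excluded from assessments". No attrition rate is given anywhere.

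**The concern.** Two features of the main model conflict with the schedule and with the limitation the authors concede.

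First, a test not given at 4 weeks has no score at one of the three time levels. The 2 x 3 model cannot be fitted to it, and the sample-size statement does not describe it.

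Second, for tests given at every visit, a classical repeated-measures ANCOVA uses only children with a score at every level of time. A child who misses one visit also loses the scores that were observed. If missed visits track severe complications, the analysed children are a selected group. The early post-transplant change is then at risk of looking milder than it is, and identifying peri-surgical neurocognitive disorders is a stated objective. The hypotheses expect improvement, so selection of healthier children can push results in the hypothesised direction.

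**Working it through.** **1. The passages side by side.** The main model has three time levels for the outcomes (3.6). The 4-week battery is shorter (3.5). All outcomes are measured at three times (Abstract). These cannot all hold for every test: a session of 45 minutes against 90 to 120 minutes implies that some tests are left out. Which ones is presumably in Figure 1, which is not shown to us.

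**2. The plan's own figure.** Repeated-measures F test for the group-by-time interaction, with k groups, m times, correlation r between times and sphericity:

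- noncentrality = f² × N × m / (1 − r)
- df1 = (k − 1)(m − 1); df2 = (N − k)(m − 1)

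From 3.6: k = 2, m = 3, f = 0.25, alpha = 0.05, power 0.95. The protocol states no r.

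- r = 0.5: N = 36 gives noncentrality 0.0625 × 36 × 3 / 0.5 = 13.5 and power 0.906; power 0.95 needs N = 44.
- r = 0.6: N = 36 gives noncentrality 0.0625 × 36 × 3 / 0.4 = 16.875 and power 0.958; power 0.95 needs N = 36.

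So 36 is reproduced at r of about 0.59 to 0.60. Without a stated r it can be neither confirmed nor called wrong, and the point does not depend on it.

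**3. Tests with two time levels (m = 2, same formula).**

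| r (assumed) | N for power 0.95 | Power at N = 36 | Power at N = 60 |
|---|---|---|---|
| 0.5 | 54 | 0.83 | 0.97 |
| 0.6 | 44 | 0.90 | 0.99 |

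At N = 60 and r = 0.5, for example, noncentrality = 0.0625 × 60 × 2 / 0.5 = 15.0 and power is 0.968.

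**4. Complete cases at all three visits.** Assume each post-transplant visit is attended independently with probability p. Complete cases are 60 × p²:

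- p = 0.85: 60 × 0.7225 = 43
- p = 0.80: 60 × 0.64 = 38
- p = 0.75: 60 × 0.5625 = 34

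**5. Illustrative selection.** Simulation of 4,000 cohorts with N = 60, equal correlations of 0.6, true 4-week change -0.30 SD, true pre-to-6-month change +0.25 SD, and one third missing at 6 months (logit slope 1 per SD).

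| 6-month dropout driven by | Quantity | True | Complete case | Likelihood, all observed scores |
|---|---|---|---|---|
| a low 4-week score | 4-week change | -0.30 | -0.19 | -0.30 |
| a low 4-week score | 6-month mean | 0.25 | 0.42 | 0.25 |
| a low 4-week score | pre-to-6-month change | 0.25 | 0.25 | 0.25 |
| a low (unseen) 6-month score | 4-week change | -0.30 | -0.30 | -0.30 |
| a low (unseen) 6-month score | pre-to-6-month change | 0.25 | 0.36 | 0.41 |

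A milder mechanism was also tried: r = 0.5, a severity variable correlated 0.3 to 0.5 with the mean of the two post-transplant scores, and the sickest 10 to 30% missing. Complete-case change from pre-transplant was then biased upward by about 0.02 to 0.07 SD at both post-transplant visits.

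**The case against.** The case for leaving the plan alone has real force on five counts.

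- **Power.** Enrolment is planned at 60, and 36 is only a minimum. At 60 the two-level tests exceed the planned 0.95, and loss could reach 1 − 36/60 = 40% before complete cases fall to 36. The result of 34 needs 25% loss at each visit, independently; missed visits caused by illness would cluster in the same children and leave more complete cases. This stands: the problem is estimability and selection, not power.
- **The 6-month result.** A reader might infer that complete-case analysis overstates improvement from pre-transplant to 6 months. When dropout follows the 4-week score and correlations are equal, that contrast is unbiased, and only the 4-week change and the 6-month level are distorted. The stronger reading is not supported in general.
- **The remedy.** If missingness follows the unseen 6-month score, the mixed model did no better on the 6-month change (0.41 against 0.36, true 0.25). This stands as a limit.
- **Wording.** The Discussion says the sickest children could be excluded, not that they are expected to miss visits. Complete-case handling is inferred from the method named; no sentence states it. Latent growth models, which can use incomplete records, are planned.
- **Unseen detail.** Figure 1 may list the 4-week tests, and nothing shows that the online questionnaires are shortened. Using two levels for omitted tests could be left to an analysis plan.

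What the objection does not remove is that the document itself fixes the main model and the schedule, and they do not match. Figure 1 could name the omitted tests, but it would not reconcile the Abstract and 3.6 with 3.5. The growth models are additional and do not change the main analysis.

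**Conclusion.** The concern holds in a limited form. The three-level main model cannot be applied to tests left out at 4 weeks, and the Abstract's statement about measurement times must be reconciled with the Procedure. For the remaining tests, the named method discards children with any missing score, in a study that concedes missingness could follow severity.

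The size of the bias is unknown because no attrition rate is given. Under the illustrated mechanisms the 4-week decline could be understated by about 0.11 SD (-0.19 against -0.30), or not at all. Pre-to-6-month change could be unbiased, or overstated by 0.02 to 0.11 SD (0.36 against 0.25 at the upper end). These figures rest on assumed correlations, dropout rates and mechanisms.

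The documents do not support a claim that the study is underpowered, that 36 is wrong, or that a mixed model would remove the bias. The change is worth making because it uses all observed scores and needs a weaker missing-data assumption than complete-case analysis.

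**What to change.** In 3.6, make a linear mixed model for repeated measures the main analysis (SPSS MIXED, in the package already named): categorical time, group, group-by-time, the planned covariates and unstructured covariance, using every observed score. Keep the complete-case mixed ANCOVA as a sensitivity analysis.

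State which tests are omitted at 4 weeks, that these use two time levels, and their power at f = 0.25: about 0.97 to 0.99 with 60 children and 0.83 to 0.90 with 36, for r from 0.5 to 0.6. Align the Abstract with this.

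The cost is wording only, with the same data and software. The model relies on data being missing at random. It does not remove bias if missingness depends on unobserved scores, so the limitation in the Discussion should stay, and it cannot give a 4-week effect for a test not given then.
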